#### Component 3: Machine Learning Algorithm

In our prior publications, we have described our algorithm development in detail [16,32,33]. For the purpose of this paper, we describe our approach and the functioning of the system in brief. We used a strong generalization protocol that involved completely separating test users from train users, learning a model using all the train users’ ratings, freezing all non–user-specific parameters, and finally training the user-specific parameters on a subset of each test user’s observed ratings. We evaluated several recommender methods for accurate prediction, including K-nearest neighbors, probabilistic matrix factorization, collective matrix factorization, and the Bayesian probabilistic matrix factorization (BPMF) [33]. In evaluating rating prediction methods, we used a range of standard performance metrics including root mean squared error, Kendall tau-b, and normalized discounted cumulative gain. In all these tests, BPMF was identified as the best single model. For example, comparing the root mean squared error metric between the different algorithms, there was a small but statistically significant gap (*P*=.01) between the BPMF and other algorithms as determined by a paired *t* test with Bonferroni correction. The BPMF model estimates a probability distribution over a joint embedding of users and items into complementary latent spaces. The rating of the given user supplies for a given item is approximated by the expected value of the product of the latent user and item factor vectors representing the user-item pair, with the expectation taken over the uncertainty in embeddings.

The intervention participant experience is as follows: during baseline registration, the intervention participant will be asked to rate 5 messages. The recommender system will use these ratings to select the first message. As the intervention unfolds, the participant will be asked to rate each message, and the system will learn and adapt to these ratings [16,32,33]. In the backend, each time the program needs to select a message for an individual, the program sends all the prior ratings provided by the participant and the messages rated by the participant. The system also sends demographic information of the participant. The algorithm then selects the next messages based on these data from the list of messages that have not been sent to the participant. The algorithm was also programmed to choose only from among those messages that matched the participant’s readiness to quit status. All participants will receive a new message every time. When they do not rate the message on a particular day, our system will have the 5 messages rated at baseline and the ratings of the prior participants to fall back upon to pick a new message. Because the machine learning algorithms operate as a black box, in our prior study, we conducted an analysis of our messages to uncover the black box of the algorithms and understand the message selection process and have published our results [35].

#### Flow of the Intervention

Participants in the intervention group receive motivational messages, texting quitline facilitation, and texting assessment of smoking status.

Motivational messages selected by the Adapt2Quit recommender system including ratings for user feedback. Participants receive daily motivational messages for the first 30 days and every 14 days until the end of the study. As noted, participants were asked to read these messages and provide their ratings. They were able to choose how frequently they rated messages.

For texting quitline facilitation, participants in both study arms were asked (via text message) if they were interested in being referred to the quitline every 14 days or until the participant responded “yes” to this question. We have followed current best practices in SMS text messaging to connect users to the quitline as described in the study by Krebs et al [36], who, after assessing multiple message frames, found that including a self-efficacy frame was the most effective. If participants request to be connected, a member of the study team refers them to quitline via a secure web form provided by the Massachusetts and Maryland quitline. As per their standard protocol, once quitline staff receive notice of participant interest, they proactively call the participant and engage in counseling.

For texting assessments of smoking status, participants were asked, “What is your current smoking status?” every 30 days over a 6-month period.

### Comparison

To isolate the effect of the Adapt2Quit recommender system, comparison participants do not receive tailored motivational messages but receive the texting quitline facilitation and the texting assessment of smoking status with the same frequency as intervention participants.

### Six-Month Data Collection Procedures

#### Overview

Six-month follow-up was conducted via telephone using the REDCap (Research Electronic Data Capture; Vanderbilt University) system to collect the data. Participants had the option to complete the REDCap survey on their own, with research staff sending the secure REDCap link by either email or text or mailing a paper survey to the participant. The system is designed to first collect the main outcome data and then branch into any intervention or control-specific questions. This way the staff is blinded to the participants’ assignment when the primary outcome data are collected. To maximize retention, participants were asked upon enrollment to provide 2 alternate telephone numbers, their physical and email addresses, and any other contact information, as applicable. All this contact information was used in making multiple attempts to reach participants to complete their follow-up assessment, which includes sending a thank you letter and incentives for completing the 6-month visit. Participants in both groups will receive a US $25 incentive for completion of the 6-month follow-up and an additional US $50 for completing the CO verification assessment. A web-based tracking system was used to automatically alert staff about participants due for the 6-month follow-up measure to facilitate timely assessments.

#### Qualitative Interviews

After completion of the 6-month follow-up visit, intervention participants will be invited to complete the qualitative interview to deepen the understanding of potential mechanisms and ways to improve the next generation of the Adapt2Quit intervention (Multimedia Appendix 1). We are using a purposeful sampling approach to recruit interview participants (n=30). Purposeful sampling is a technique widely used in qualitative research for the identification and selection of information-rich cases for the most effective use of limited study resources [37]. We will select participants based on the extent of engagement with Adapt2Quit, use of the quitline, and eventual quitting success. Study coordinators will contact participants who agree to be interviewed to complete the audio-recorded qualitative interviews. The interviews will be conducted by phone and will examine a series of topics following the hypothesized path model presented in the research strategy (Adapt2Quit increases engagement, which results in external and internal processes causing the participant to implement smoking cessation–supporting behaviors; Multimedia Appendix 1). Across these topics, our goal is to understand what participants value most and to elicit recommendations for further system enhancement. Interviews are semistructured, allowing for natural conversation with opportunities to explore unanticipated issues, and will be no longer than 30 to 45 minutes in duration. All qualitative interview participants will be asked to provide verbal consent before participating in the interview and being audio recorded. For participation in the qualitative interview, participants will receive US $50.

### Data Elements, Statistical Analysis, and Power Calculation for Specific Aims

Data are collected throughout the study at several time points via text-based ratings, quitline use, assessments, questionnaires, and CO readings. Our main outcomes are described subsequently.

#### Completion of Ratings

Each Adapt2Quit message is accompanied by the influence ratings question as follows: “Please type the number below to indicate whether you agree with this statement—How much does this message influence you to quit smoking”—on a 5-point Likert scale (strongly disagree to strongly agree). Our program tracks the ratings completed for each participant.

#### Internal Processes

Perceived competence, a key SDT construct, will be measured using the previously validated PCS [23]. The 4-item scale assesses the participant’s feelings of being able to stop smoking permanently (“I feel confident in my ability to not smoke,” “I now feel capable of not smoking,” “I am able to not smoke anymore,” and “I am able to meet the challenge of not smoking”). Responses are scored on a 7-point scale from 1 (strongly disagree) to 7 (strongly agree), and individual items are averaged to create a scale mean. In prior work [23], PCS was reliable (α=.95) at the 6-month follow-up [23]. We will assess PCS at baseline and at the 6-month follow-up visit.

#### External Processes (Quitline and NRT)

Quitline use is assessed using data collected from the quitline. We will send a list of our users and ask quitline to provide data on these users, such as the number of contacts between the smoker and the counselor. We will use the time to first call completed with the quitline counselor as our primary quitline measure. NRT is self-reported (yes or no).

#### Six-Month Cessation

Assessment of the 6-month smoking cessation is collected using the 7-day point-prevalence question [38]: “Do you currently smoke cigarettes (smoked even 1 puff in the last 7 days)?” Point prevalence can capture an intervention’s delayed effects. A psychometric analysis comparing continuous, prolonged, and point-prevalence outcomes found that point prevalence had the highest concurrent validity [38]. The 7-day window provides an appropriately stringent measure to account for a cross-sectional snapshot. Using the CoVita Smokerlyzer breath CO monitor, participants who self-report quitting at the 6-month follow-up will be asked to complete biochemical verification remotely (the device will be mailed to them) or in person. Because of the variability of the device, participants will be asked to repeat the test 3 times. The average of these values will be used for our analyses [39]. Participants will be classified as tobacco users if their CO measurement is >6 ppm [40]. Participants completing remotely will be asked to conduct the test over videoconference, where our staff will monitor and guide them. To complete the biochemical verification, whether in person or remotely, study participants will receive a US $50 gift card.

### Data Analysis

#### Statistical Analysis and Power Calculations

To preserve randomization, all primary analyses will be on an intent-to-treat basis. Secondary analyses will explore dose-response effects among those with variable levels of adherence to the intervention. All analyses will be 2-sided, and the α error level will be set at .05. We will begin by examining univariate statistics (means, medians, SDs, frequencies, percentages, and 95% CIs) and distributions of the variable of interest. We will examine the balance of participant characteristics by study groups and account for any imbalances in our multivariable analysis. To address sex as a biological variable, we will stratify the analyses by male and female to evaluate whether the mechanisms and outcomes are modified by sex. We will test group differences either using chi-square tests of independence (categorical variables), *Z* test, or a 2-tailed *t* test (continuous variables), or the equivalent nonparametric tests depending on the distribution of the variables. Baseline differences between the intervention and control group will be established based on standardized differences, rather than on tests of statistical significance.

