##### Power for Primary Outcome (Hypothesis 3a)

In our prior National Cancer Institute trial, we observed an absolute 9% difference in the standard messaging versus no-messaging control group [29]. We expect socioeconomically disadvantaged groups to have lower cessation rates than non–socioeconomically disadvantaged groups. Thus, we calculated power using a range of control cessation rates from 7% to 9%. We started at 7%, because it is the estimated rate at which the general population of all individuals who smoke quit without any intervention [34]. On the basis of the recommender enhancements (and further pilot data), we saw an additional marginal difference of 6% at 30 days (even higher for African American individuals who smoke) and expect this difference to continue and expand over time as the recommender system continues to learn and adapt to the individual; however, to be conservative and recognizing the potential difficulty in impacting behavior in this population, we chose to power for a small difference, namely 7%. Although our hypothesis is directional, we have chosen to adopt the commonly used conservative approach of 2-sided tests for all our power calculations. On the basis of a 2-sided chi-square test of equal proportions, α=.05, for all these base rates, we will have 80% power with 600 participants (N=300 per arm). Considering loss to follow-up, we plan to oversample by 25% and thus have budgeted for a total of 750 participants to complete baseline and be randomized. On the basis of our prior experience recruiting from clinical systems, we expect the dropout rate to be lower than the 25% we have assumed in our calculations.

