### Conclusions and Future Work

Our project is the first to rigorously test the use of a recommender system for smoking cessation among individuals from socioeconomically disadvantaged backgrounds who smoke. In this paper, we have reported on protocols for conducting a rigorous trial. In addition to our primary analyses for the 3 aims, we will conduct exploratory analyses to assess the heterogeneity of treatment effects across these subgroups, which could yield valuable insights for future tobacco cessation efforts. Our follow-up papers will report on the results of our trial following the analysis plans described in this paper. Future studies will also explore implementing texting interventions in various clinical and public health settings.

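### Modification by sex is to be judged from separate male and female analyses, which test the effect within each sex but not the difference between the sexes

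*Protocol article*

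**What the plan says.** The protocol article, under Statistical Analysis and Power Calculations, states a purpose and a method in one clause: "we will stratify the analyses by male and female to evaluate whether the mechanisms and outcomes are modified by sex". The same paragraph sets the error level for everything: "All analyses will be 2-sided, and the α error level will be set at .05". It goes on to list tests of group differences. No later section (Hypotheses 1a to 3b) adds an arm-by-sex term, a contrast between the two strata or a criterion for concluding that sex modifies an effect. Power is stated for the overall primary comparison, for two perceived-competence hypotheses and by cross-reference for quitline use, but not for either sex or for an interaction.

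**The concern.** The question is whether the effect differs between men and women. Stratified analyses answer two other questions: whether there is an effect in women, and whether there is one in men. A result that is significant in one stratum and not in the other can arise from chance and unequal stratum size alone. Here the strata are unequal, since 486 of 757 participants are female.

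Sex is the only effect modifier named in the analysis section, and the clause covers both mechanisms and outcomes. The same weakness would therefore recur for the Perceived Competence Scale (PCS), quitline use, nicotine replacement therapy (NRT) and cessation. At stake is a possible published statement that the intervention works in one sex only, when the data do not show that the sexes differ.

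**Working it through.** **Inputs**
- Two-sided α = .05 (Statistical Analysis and Power Calculations).
- Chi-square test of two proportions, control cessation 7% to 9%, absolute difference 7 points, 300 evaluable per arm (Power for Primary Outcome).
- 1:1 allocation (Randomization).
- Female share 486/757 = 64.2% (Abstract, Results).
- Assumption: the remainder are male, and the split is the same in both arms and among those with outcome data.

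**Formula.** With n per arm, rates p1 and p2, and mean rate p̄:
- s0 = √(2p̄(1−p̄)/n)
- s1 = √((p1(1−p1) + p2(1−p2))/n)
- power = Φ((p2 − p1 − 1.96·s0)/s1)

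**The plan's own figure first.** For 7% vs 14% with n = 300, s0 = 0.02503 and s1 = 0.02487. So z = (0.07 − 0.04906)/0.02487 = 0.842 and power is 80.0%, as stated. At control rates of 8% and 9% the same formula gives 76.8% and 73.8%. The stated 80% is thus met only at the low end of the range, which does not alter the present point.

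**Power within each sex.** 300 × 0.642 ≈ 193 women and 107 men per arm. At a 7% control rate:
- Women: s0 = 0.03121, s1 = 0.03100, z = 0.285, power 61.2%.
- Men: s0 = 0.04191, s1 = 0.04164, z = −0.292, power 38.5%.

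**Chance that exactly one sex is significant when the effect is identical.** The strata are independent, so this is Pw(1 − Pm) + Pm(1 − Pw), where Pw and Pm are the powers in women and men. At 7%: 0.612 × 0.615 + 0.385 × 0.388 = 0.376 + 0.149 = 0.526.

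| Control rate | Power, women | Power, men | Women only | Men only | Exactly one |
|---|---|---|---|---|---|
| 7% | 61.2% | 38.5% | 37.6% | 14.9% | 52.6% |
| 8% | 57.8% | 36.0% | 37.0% | 15.2% | 52.2% |
| 9% | 54.8% | 33.9% | 36.2% | 15.3% | 51.5% |

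Simulation (400,000 trials per row) gives 52.5%, 52.3% and 51.5%. With the 591 participants followed up by May 2024 the figure is 51.3% to 52.5%, and with all 757 it is 51.4% to 52.6%. Across these sample sizes women only is about 36% to 38% and men only about 13% to 16%.

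**Dependence on the true common effect** (8% control, 193 and 107 per arm, simulated):

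| Common effect | Exactly one sex significant |
|---|---|
| 0 points | 10% |
| 2 points | 17% |
| 3 points | 25% |
| 5 points | 42% |
| 9 points | 49% |

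Over control rates of 7% to 9%, the 2- and 3-point rows together span about 16% to 26%.

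**A direct test for comparison.** In the same simulations, a Wald test of the female-minus-male difference in risk difference rejects in 5.1% to 5.2% of trials when the effect is the same in both sexes, whatever its size.

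**Precision of that contrast.** At 7% vs 14% the variance of one stratum's risk difference is (0.0651 + 0.1204)/n. The standard error of the contrast is √(0.1855/193 + 0.1855/107) = 0.052, so the 95% CI half-width is 1.96 × 0.052 ≈ 10 percentage points. That is wider than the whole planned effect, so a direct test has low power.

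**The case against.** A reader might infer that the plan will declare modification whenever one sex is significant and the other is not. The text does not say so. It says the analyses will be stratified in order to evaluate modification, which is compatible with comparing estimates and confidence intervals. The general α of .05 is not a decision rule for sex. This stands: the 52% is the consequence of one natural reading, not of a rule in the protocol.

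A reader might also infer that discordance occurs about half the time whatever the truth. It does not. The figure belongs to an identical effect near the planned 7 points and falls to about 10% when there is none. Nor is a false claim the likely result. Even at 7 points, significance in women only is a minority outcome, and discordant p-values become a claim only if someone reads them that way.

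It can be said that an interaction term is detail for the statistical analysis plan, which is not shown. That would hold if the article left the method open. Here it names one, and that method does not answer the question set. The argument does succeed for Conclusions and Future Work, where the authors write "we will conduct exploratory analyses to assess the heterogeneity of treatment effects across these subgroups". That sentence names no method and is labelled exploratory, so it is not part of the error.

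Finally, sex belongs to no listed hypothesis, and the primary conclusion rests on the overall weighted comparison. Both points are correct and limit the stakes.

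**Conclusion.** The concern holds as a mismatch between a stated purpose and a stated method. Stratifying by sex does not estimate or test the difference between the sexes, and nothing else in the article does.

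If the stratum tests are read side by side, an identical 7-point effect would look sex-specific in about 52% of trials, against about 5% false positives for a direct contrast. With no effect in either sex the figure is still about 10%. These numbers rest on 300 evaluable per arm, control cessation of 7% to 9%, and a 64/36 sex split that is equal by arm and among completers. They are computed for unweighted proportions, not for the weighted logistic model.

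The plan could invite a false sex-specific claim; the documents do not show that it will make one. The primary comparison is not affected. This should be corrected, but it is a secondary matter.

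**What to change.** In Statistical Analysis and Power Calculations, replace stratification as the means of judging modification:

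- Add an arm-by-sex interaction term to the weighted logistic model for cessation and to the between-arm models for PCS, NRT and quitline use.
- Base any statement about modification by sex on that estimate and its 95% CI.
- Present the sex-specific estimates as descriptive.
- State that the interaction has low power and that a nonsignificant result is not evidence that sex makes no difference.

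The cost is one term per model and a sentence or two of text. No data collection or sample size changes. The small downside is the low power itself: the interval will be wide, and the trial may be unable to say much about sex either way.

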#### Aim 1: Adapt2Quit Engagement

Aim 1 is analyzed within the intervention group (N=375). Engagement will be defined as the number of daily ratings divided by the total number of rating opportunities (percentage of ratings completed).

##### Hypothesis 1a

Among Adapt2Quit participants, those with higher engagement levels (completed more ratings) will have greater scores on the PCS. For hypothesis 1a, we will explore the distribution of the PCS at baseline and the averaged PCS scores during follow-up. Furthermore, we will analyze the distribution of engagement. It is likely that these distributions will be nonnormally distributed. In this case, we will transform the distribution into something approximating normality or choose a nonparametric test to assess the correlation between engagement and the PCS. We will generate a generalized linear model with the averaged follow-up PCS score as the dependent variable and engagement as the independent variable, adjusting for demographic characteristics that vary between highly engaged and less-engaged individuals and for baseline PCS measurements.

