**Results:**

The Adapt2Quit study was funded in April 2020 and is still ongoing. We have completed the recruitment of individuals (N=757 participants). The 6-month follow-up of all participants was completed in November 2024. The sample consists of 64% (486/757) female participants, 35% (265/757) Black or African American individuals, 51.1% (387/757) White individuals, and 16% (121/757) Hispanic or Latino individuals. In total, 52.6% (398/757) of participants reported having a high school education or being a high school graduate; 70% (529/757) smoked their first cigarette within 30 minutes of waking, and half (379/757, 50%) had stopped smoking for at least one day in the past year. Moreover, 16.6% (126/757) had called the quitline before study participation.

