### Theoretical Basis for the Adapt2Quit Intervention

The Adapt2Quit intervention is based on the self-determination theory (SDT). SDT-based interventions support autonomous decisions and are designed to increase intrinsic motivation and self-regulation and they have been shown to improve motivation and cessation outcomes among those who smoke [19-24]. Three innate psychological needs are theorized to promote self-motivation: autonomy, relatedness, and competence [19]. Autonomy reflects the need to engage in behaviors with a sense of choice or personal endorsement [25]. Autonomy support can be provided by acknowledging an individual’s unique perspective and offering choice [25,26]. Relatedness reflects the degree to which an individual feels connected to and understood by others. Competence is a feeling of being capable and is akin to self-efficacy, the belief that one can bring about desired outcomes. By supporting autonomy, relatedness, and competence, health behaviors are more likely to be internalized and maintained. Specific examples of how Adapt2Quit supports the SDT are provided in Textboxes 1 [27] and 2. Our aims and hypotheses align with our proposed model, which suggests that relevant personal messages from the Adapt2Quit system will enhance system engagement. This increased engagement is expected to improve internal processes (ie, the SDT constructs measured using the Perceived Competence Scale [PCS]), leading participants to adopt cessation-supporting behaviors (external processes such as quitline and nicotine replacement therapy [NRT] use), ultimately resulting in smoking cessation.

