#### Component 2: Ratings Database

The algorithm uses 2 types of ratings data to generate the following recommendations.

First, ratings from prior study participants. More than 1000 participants have rated our messages using the influence rating question (see definition in the Data Elements, Statistical Analysis, and Power Calculation for Specific Aims section) resulting in 18,920 ratings [16,32,33]. We chose the influence rating question after a pilot test in which we asked participants to rate each message on 4 aspects: influence, emotional response, relevance, and preference [33]. We found that all these aspects were highly correlated. In developing the algorithms for the recommender system, we compared ratings by different user profile characteristics. Of the 20 messages rated most highly by participants with less than a high school education, only 3 messages were rated in the top 20 by college graduate participants. Adapt2Quit considers all these variations for message selection.

Second, current ratings from participants in the intervention group using 2-way texting. Adapt2Quit is also programmed to learn from the explicit ratings of participants receiving the messages. Thus, when a participant is sent a text message, it will be accompanied by a question (see definition in the Data Elements, Statistical Analysis, and Power Calculation for Specific Aims section) asking the participant to rate the text message using the influence ratings question. The participant can choose how frequently they wish to rate the text messages. In addition to improving the system, our participants in the pilot studies noted that rating the messages helped them to cognitively process the messages better and remember their content.

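### Hypothesis 1a compares self-selected engagement levels but leaves readiness to quit and nicotine dependence out of its stated adjustment, so residual confounding can produce a spurious association with perceived competence

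*Protocol article*

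**What the plan says.** Under Hypothesis 1a, the protocol article specifies a "generalized linear model with the averaged follow-up PCS score as the dependent variable and engagement as the independent variable". The covariates for that model are set out in the same sentence, and the rule for choosing them reads: "adjusting for demographic characteristics that vary between highly engaged and less-engaged individuals and for baseline PCS measurements". No other covariate is named for this model.

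The section on Aim 1 defines engagement as "the number of daily ratings divided by the total number of rating opportunities" and confines the analysis to the intervention arm, with 375 participants planned. Component 2: Ratings Database states: "The participant can choose how frequently they wish to rate the text messages".

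The article shows that relevant smoking variables are held:
- **Readiness to quit.** Component 3 describes a filter that uses each person's readiness status: "The algorithm was also programmed to choose only from among those messages that matched the" (the sentence then names that status).
- **Dependence.** The abstract's results give the share of participants who "smoked their first cigarette within 30 minutes of waking" (529 of 757). They also report past-year quitting and earlier quitline calls.
- **Motivation.** The Discussion describes participants as more motivated than the general population.

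The theoretical section gives the link a causal direction: "This increased engagement is expected to improve internal processes". The same link is a step in the path model described under Hypothesis 3b.

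**The concern.** Randomisation does not protect a comparison between people who chose to rate many messages and people who chose to rate few. Someone more ready to quit, or less dependent, may plausibly both answer more texts and feel more able to stay off cigarettes at six months. If so, the two measures will be correlated without rating having done anything.

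The stated rule addresses this poorly in two ways. It limits adjustment, beyond baseline PCS, to demographics, when the likelier confounders are motivation and dependence. It also admits a demographic variable only if it differs by engagement level in the data at hand, which makes the model data-dependent and ignores whether the variable predicts PCS.

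What is at stake is the reading of the first link in the trial's proposed mechanism, not its effectiveness result.

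**Working it through.** **1. The plan's own figure.** Power for Hypothesis 1a claims 80% power for a correlation of 0.2 with 200 patients, at the 2-sided .05 level set for all analyses. By Fisher's z, power = Φ(atanh(r)·√(n−3) − 1.96).
- n = 200: atanh(0.2) = 0.2027, √197 = 14.04, so Φ(2.846 − 1.96) = 81.2%. The claim reproduces; 194 patients would give 80%.
- n = 375: 97.4%, consistent with the article's statement that power is well above 90%.

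There is no arithmetic error here.

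**2. Is the gap filled elsewhere?** Statistical Analysis and Power Calculations promises to account for imbalances, but between the randomised study groups, not between engagement levels. Nothing else in the article adds readiness or dependence to this model.

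**3. Sample size.** The Results report 591 of 757 (78.1%) followed up as of May 2024. Assuming the same rate in the intervention arm, 0.781 × 375 ≈ 293. Final completion may be higher, so 375 is shown as the ceiling.

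**4. Spurious correlation.** Suppose engagement has no effect. Let an omitted variable have partial correlation *a* with engagement and *b* with follow-up PCS, both given baseline PCS. The model as planned then sees a partial correlation r = a·b. With m = atanh(r)·√(n−4), the probability of a significant result is 1 − Φ(1.96 − m) + Φ(−1.96 − m).

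Worked case, a = b = 0.3 and n = 293: r = 0.09, m = 0.0902 × 17 = 1.534, so 1 − Φ(0.426) + Φ(−3.494) = 33.5%.

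The values of *a* and *b* are assumptions; the article gives none.

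| a, b | r = a·b | n = 293 | n = 375 |
|---|---|---|---|
| 0.1, 0.1 | 0.01 | 5.3% | 5.4% |
| 0.2, 0.2 | 0.04 | 10.4% | 12.0% |
| 0.2, 0.3 | 0.06 | 17.5% | 21.2% |
| 0.3, 0.3 | 0.09 | 33.5% | 41.2% |

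**5. Simulation check.** With 4,000 simulated data sets per setting at n = 293 and baseline PCS in the model, rejection was 10.2% at 0.2/0.2 and 33.0% at 0.3/0.3. With the omitted variable added it was 4.6% and 5.0%.

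**The case against.** The strongest reply is that little is claimed for this analysis. It is worded as a correlation within one arm, and its power section places it among secondary analyses. The causal sentence belongs to the theory background. Baseline PCS, which is the outcome's own baseline value and measures confidence in not smoking, is already in the model and absorbs part of motivation.

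Most of this stands, and it limits the point. Only confounding that remains after baseline PCS adjustment counts, and its strength is unknown. At 0.1/0.1 there is almost no inflation. In a simulation where readiness overlaps more with baseline PCS (correlation 0.6 rather than 0.4), the rates fall to 8–9% at 0.2/0.2 and 22–27% at 0.3/0.3. The spurious correlations in the table, at most 0.09, are also well below the 0.2 on which power was based.

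A reader might infer that a positive Hypothesis 1a result is to be expected even if rating does nothing. The article does not support that: it gives no correlation of readiness or dependence with engagement or with PCS. A spurious link can arise; whether it will is not known.

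A reader might also take the return to about 5% as proof that adjustment cures the problem. That result is built into a simulation with one confounder, perfectly measured. Early quitting or rising confidence during follow-up could itself drive rating, and no baseline covariate removes that.

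The reply that covariate lists belong in a separate analysis plan does not answer the point. The article states an adjustment rule, and its closing section says later papers will follow the analyses it describes.

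**Conclusion.** The point holds in a limited form. The stated adjustment for a non-randomised, within-arm comparison leaves out readiness to quit and dependence, although the trial records both, and it selects demographics by their observed difference. The resulting false-positive rate is about 5%, 10% or 33% for assumed partial correlations of 0.1, 0.2 or 0.3 on both sides, with about 293 completers and no true effect. These figures show what could happen; they do not estimate what will. A significant Hypothesis 1a result from the planned model would be weak support for the engagement step of the mechanism. The randomised comparisons of PCS (Hypothesis 2a) and cessation (Hypothesis 3a) are untouched. This is worth correcting because the correction costs almost nothing, not because the trial's main conclusion depends on it.

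**What to change.** In Hypothesis 1a, replace the rule that selects demographics by whether they differ with a covariate set fixed in advance and entered regardless of any difference by engagement:
- baseline PCS;
- baseline readiness to quit;
- a dependence marker, for which time to first cigarette is available;
- the core demographics.

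The article does not say when the readiness status used by the algorithm was recorded, so confirm that a baseline value exists and use that one.

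State that the result will be interpreted as an association, and that reverse causation (early quitting or growing confidence leading people to rate more) remains after adjustment.

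The cost is analysis wording and a few degrees of freedom out of roughly 290 participants, with no new data collection. The article expected analysis in late 2025. If it has begun, label the fuller model as added and report it beside the planned one.
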